**Fig. 3 Fig3:**
[figure not shown]
Study design. Figure 3 illustrates the design of the study, highlighting the comparison of the two study groups at different time points

### Study population: eligibility criteria

#### Inclusion criteria

To be eligible for participation, subjects are required to fulfill the following criteria:age between 2–17 yearsinformed consentchronic constipation according to the ROME IV criteria for more than 3 months with abdominal pain and with or without FI [12] despite underlying diseases such as FC, rectal evacuation disorders or HD.refractory to conventional treatment in an appropriate weight-adapted application (training for bowel movements, lifestyle changes, pelvic floor training, pharmacological options)in cases of HD: diagnosis confirmed histologically by rectal biopsies and in case of resection of an aganglionic segment: period between surgery and SNM at least 1 yearin cases of anorectal malformation or mechanical obstruction: post-surgical status: period between surgery and SNM at least 1 year

#### Exclusion criteria

Exclusion criteria are determined as follows:metabolic, inflammatory, and hormonal causes for chronic constipationtoxic megacolon or further emergencies, which must be treated surgicallysacral fractures or malformations prohibiting SNM access to target nervesinflammatory bowel diseasesexternal rectal prolapseneuronal malignancies under medical and radiation therapyseizures

### Recruitment

Participants are recruited from the outpatients and inpatients clinics of the pediatric surgery and gastroenterology departments. Two or more experts determine the eligibility according to the inclusion and exclusion criteria. Informed consent, especially on treatment modalities and off-label use of SNM/ENM in childhood and adolescence, must be obtained before enrollment in the trial by next-of-kin and participants (6 years and older). Thereafter, a baseline assessment is performed, collecting all baseline information relevant to the study (sociodemographic data, medical history, current defecation status). The study schedule is summarized in Fig. 4 and included as the SPIRIT template as Fig. 5. At all timepoints, patients are able to withdraw their participation and end therapy with neuromodulation.

**Fig. 4 Fig4:**
[figure not shown]
Study schedule. Figure 4 explains evaluation of outcome variables at different time points of the study

**Fig. 5 Fig5:**
[figure not shown]
SPIRIT figure. Figure 5 summarizes the schedule of enrolment, interventions, and assessments according to the SPIRIT figure

### Randomization

Participants are enrolled in the study groups at a 1:1 allocation to either the SNM or ENM group. Furthermore, patients are allocated 1:1 stratified based on HD/FC. Enrollment of subjects (assessment of eligibility, patient contact to obtain informed consent) is done by investigators and clinicians prior to randomization. The study design does not allow blinding of the therapist or further analyses in clinical follow-ups. The design is open label with only outcome assessors being blinded, so unblinding will not occur. Data analysis and statistical assessment are conducted separately and anonymously. The statistician performing the statistical analyses is blinded to individual group allocation and treatment.

### Interventions

#### Non-pharmacological treatment in both study groups

All subjects are provided with non-pharmacological management counseling prior to the study inclusion, including lifestyle modifications, such as (1) age-appropriate fluid consumption, (2) balanced diet and (3) regular sportive activity (at least 3 × 30min per week). Education and conduction of toilet training is further advised to improve regular bowel movements. If patients show further symptoms, irresponsive to these measurements, enrollment is conducted and non-pharmacological treatment is continued throughout the trial.

#### Pharmacological treatment in both study groups

Pharmacological options are included in the study population as follows: disimpaction with polyethylene glycol (PEG, 1.5-2mg/kg/d for 1–2 weeks) and initiation of maintenance therapy (PEG, 0.2–0.4 mg/kg/d) are conducted prior to the study inclusion. Maintenance therapy is continued throughout the study period in both groups. Supportive local applications such as saline enemas or stimulant laxatives (glycerin, bisacodyl) are applied as needed. Change of pharmacological treatment is not recommended during the study period, especially in case of rectal enemas. Medication due to other diagnoses is not changed during the study period.

#### Group 1: enteral neuromodulation

ENM is continuously applied for 12 weeks in each patient. Stimulation intensity is individually set by each patient to achieve a comfortable stimulation below pain threshold.

#### Group 2: sacral neuromodulation

With the implantation of the electrode, stimulation of S3/4 is continuously applied. Patients are able to set stimulation intensity parameters within a preset range via an external device with or without the IPG.

### Statistical methods

#### Objectivation and data validation

Specialized questionnaires were developed to objectivize symptoms and medical history of patients. These include sociodemographic data, medical history, and current defecation status and were adjusted for time points of “Baseline”, “Treatment with ENM” and “Treatment with SNM”.

Quality of life data are assessed according to the ‘Revised Children’s Quality of Life Questionnaire’ (KINDL^R^) before and after treatment. This reliable and validated questionnaire is a self-report measurement for health-related quality of life in children and adolescents [13, 14]. It consists of 24 5-point Likert-scale items, covering 6 quality of life dimensions: physical well-being, emotional well-being, self-esteem, family, friends, and daily functioning (school or nursery school/kindergarten). Items are partially reversely scored and linearly transformed to a 0 to 100 scale according to the manual. The sub-scales of these six dimensions are combined to produce a total score. Higher scores indicate a better quality of life. The questionnaire is available in three age-specific versions (The Kiddy-KINDL^R^ for 4–7 years of age, the Kid-KINDL^R^ for 8–12 years of age and the Kiddo-KINDL^R^ for 13–16 years of age).

#### Data collection

Data is extracted from the bowel movement diaries and specialized questionnaires. Recorded data is stored in case report forms at a secured place. Data is coded and entered in electronical files using Excel 2007 software (Microsoft Cooperation) by at least 2 different data administrators to reduce mistakes. All files are protected with password, which is only known by the investigators. Only the investigators have access to the final trial dataset. The information of the grouping and the results of the study are provided to the participants after the trial. Publications will only report aggregated data, and personal identities will not be disclosed.

#### Sample size calculation

As there is still insufficient clinical evidence on neuromodulation treatment in children and adolescents with FC and HD, this study requires only a small sample size. Power analysis is based on abdominal pain as primary outcome variable. A minimum of 78 subjects in total and 39 subjects per group is powered to detect a difference of at least 30%, with a 95% confidence interval (α = 0.05) and statistical power of 80% (β = 0.2).

#### Statistical analysis

IBM SPSS version 28 (IBM, Armonk, NY) is used to perform statistical analyses by an independent and blinded statistician. Continuous variables are presented as mean ± standard deviation, categorical data are reported as frequencies and percentages. If data losses occur during the study, the last observation is carried forward to adjust the missing data in follow-up evaluations. If large amounts of data are missing in one patient, the patient will be excluded from the study based on the decision of the project management group. If participant’s withdrawal is observed in a high number of patients, protocol modifications will be made in regular meetings. We compare clinical outcome data using chi-square and Fisher’s exact tests at defined time points pre- and post-treatment in both groups. Quality of life data is compared using unpaired or paired, two-tailed sample t-tests, if applicable. In case of multiple analyses, adjustment of p-values will be conducted accordingly. We set the confidence interval to 95% and all p-values less than 0.05 are considered indicative of statistical significance.

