**Methods:**

A monocentric, randomized, unblinded, parallel-group trial is conducted. SNM is conducted in the invasive variant and in an innovative, external approach with adhesive electrodes (enteral neuromodulation, ENM). We include patients with constipation according to the ROME IV criteria and refractory to conventional options. Patients with functional constipation and Hirschsprung’s disease are able to participate. Participants are allocated in a 1:1 ratio to either SNM or ENM group. Clinical data and quality of life is evaluated in regular check-ups. Neuromodulation is applied continuously for 3 months (end point of the study) with follow-up-points at 6 and 12 months. Findings are analyzed statistically considering a 5% significance level (*p* ≤ 0.05). Outcome variables are defined as change in (1) episodes of abdominal pain, (2) episodes of FI, (3) defecation frequency, (4) stool consistency. Improvement of proprioception, influence on urinary incontinence, quality of life and safety of treatment are assessed as secondary outcome variables. We expect a relevant improvement in both study groups.

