#### Primary outcomes and measurement

Primary outcome variables are defined, and change is measured between time points of baseline, 3 and 6 months of therapy as follows:Episodes of abdominal pain: Number of episodes of abdominal pain per weekDefinition of success: reduction by at least 50% of episodes per weekEpisodes of FI: Number of episodes of FI per weekDefinition of success: reduction by at least 50% of episodes per weekDefecation frequency: Number of bowel movements per weekDefinition of success: doubling of episodes per week to at least 3 or more bowel movements per weekStool consistency: Daily assessment of Bristol Stool Scale [16]Definition of success: change of at least 2 points within the scale of 1-7

Patients are classified based on treatment response and efficacy. A “clinically relevant” improvement is defined in cases with at least 2/4 fulfilled criteria, in which symptom control or -reduction is achieved.

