#### Secondary outcomes and measurement

Secondary outcome variables are defined as follows:Improvement of proprioception: as mentioned in the specialized questionnairesEpisodes of urinary incontinence: the number of episodes per week is evaluated with the criterion for a clinically relevant improvement in cases of reduction by at least 50% of episodes per week.Quality of life: assessment based on the KINDL^R^ questionnairesSafety of treatment: adverse events as mentioned in the specialized questionnaires

FI is diagnosed at the age of ≥ 4 years in cases of prior adequate toilet training and urinary incontinence at the age of ≥ 6 years with at least 4 episodes per week.

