### Safety analysis and adverse events

Former studies on neuromodulation confirm a good safety profile. The participants conduct self-administered neuromodulation therapy at home. The participants are informed about potential adverse events and if any occur, they are instructed to terminate therapy and to immediately communicate with the researchers. Safety problems are reported to the clinical authorities (head of department, ethics committee) as well as to the manufacturers themselves. Appropriate treatment changes are then initiated. Adverse events are additionally recorded as part of the data collection for each session and will be reported to the clinical authorities and the manufacturers.

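### Last observation carried forward is the only imputation rule, and it fills missing month-6 and month-12 values with end-of-treatment values, so relapse is assumed away

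*Protocol article*

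**What the plan says.** The Statistical analysis section states: "If data losses occur during the study, the last observation is carried forward to adjust the missing data in follow-up evaluations". The next sentence adds a second rule, at the discretion of the group that manages the trial: "If large amounts of data are missing in one patient, the patient will be excluded from the study based on the decision of the project" (the quote is cut there). It gives no threshold. These are the only two rules for missing data. Clinical outcomes are then compared by chi-square and Fisher's exact tests, and quality of life by t-tests.

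On timing, the Abstract says "Neuromodulation is applied continuously for 3 months (end point of the study) with follow-up-points at 6 and 12 months". Group 1: enteral neuromodulation says "ENM is continuously applied for 12 weeks in each patient". Trial design also describes 3 months of either therapy. Under Primary outcomes and measurement, however, "change is measured between time points of baseline, 3 and 6 months of therapy".

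Stopping is foreseen. Under Recruitment, "patients are able to withdraw their participation and end therapy with neuromodulation" at any time. Under Safety analysis and adverse events, participants are told about possible adverse events and, "if any occur, they are instructed to terminate therapy". Success for pain episodes is a "reduction by at least 50% of episodes per week" (the article uses the same words for faecal and urinary incontinence). Stopping treatment plays no part in that definition.

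**The concern.** Carrying the last value forward assumes that nothing changes after the last visit attended. Two features of this trial make that hard to defend.

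- **Values cross the end of treatment.** If stimulation ends at about month 3, a child missing at month 6 or 12 is scored on a value taken under treatment. Whether benefit persists without stimulation is what the later visits could show, and the rule answers it by assumption.
- **Last values may be on-treatment values.** If the rule also covers month 3, a child who had improved at the week-4 check-up, stopped and was then lost is scored at month 3 on the week-4 value.

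The arms differ in kind: two surgical interventions against adhesive electrodes. Equal dropout for equal reasons cannot be presumed, so the comparison of SNM with ENM could be shifted. The filled-in values also enter the tests as if observed, so intervals are too narrow.

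**Working it through.** **Yardstick.** The Sample size calculation gives 39 per group for a difference of 30%, α = 0.05 and 80% power. It states no base rates. Reading 30% as percentage points, 50% against 80% reproduces it (two-sided, pooled variance):

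n = [1.96 × √(2 × 0.65 × 0.35) + 0.842 × √(0.5 × 0.5 + 0.8 × 0.2)]² / 0.30² = (1.322 + 0.539)² / 0.09 ≈ 38.5, so 39.

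This figure serves only as a scale for the biases below.

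**Months 6 and 12, ENM arm.** Let p be month-3 success, f the share missing at month 6 (assumed unrelated to relapse) and r the share of month-3 responders who relapse.

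- True month-6 success: p(1 − r)
- With values carried forward: p(1 − r)(1 − f) + pf
- Overstatement: p × f × r

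The upper value of p is the 86% improvement with ENM that the Discussion reports from the group's earlier trial. The lower value is 86 − 30 = 56%. Both f and r are assumed.

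| p | f | r | Overstatement (points) |
|---|---|---|---|
| 0.56 | 0.10 | 0.25 | 1.4 |
| 0.56 | 0.20 | 0.50 | 5.6 |
| 0.86 | 0.20 | 0.50 | 8.6 |
| 0.86 | 0.30 | 0.50 | 12.9 |

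**Month 3, if the rule reaches it.** Let q be the share of an arm lost after stopping, s their response at the last on-treatment observation and t their true month-3 response. The bias in that arm is q × (s − t). All three are assumed: s = 60–70%, t = 20–30%.

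- q = 10%: 0.1 × (0.6 − 0.3) = 3 points, to 0.1 × (0.7 − 0.2) = 5 points
- q = 20%: 0.2 × 0.3 = 6 points, to 0.2 × 0.5 = 10 points
- q = 30%: 0.3 × 0.3 = 9 points, to 0.3 × 0.5 = 15 points

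At q = 20% this is 0.06 × 39 = 2.3 to 0.10 × 39 = 3.9 patients in one arm.

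**Effect on the difference between arms**, with the same s and t in both:

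- 20% against 10% lost: (0.2 − 0.1) × 0.3 = 3 points, to (0.2 − 0.1) × 0.5 = 5 points, in favour of the arm with more loss
- equal loss: 0 points

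**The sign can reverse.** If only a baseline value exists, change is set to zero, so s = 0. With t = 20–30% and q = 20%, the arm is understated: 0.2 × (0 − 0.2) = −4 points, to 0.2 × (0 − 0.3) = −6 points.

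**The case against.** Several points on the other side carry weight.

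- **Stopping is not the same as missing.** A reader might infer that every child who stops keeps an on-treatment success. The article does not support that. Trial design promises efforts to obtain observations after withdrawal, and a child still seen at month 3 is scored on the value found there. The safety section also foresees treatment changes after an adverse event, so a stop need not be permanent or lead to dropout. This stands and limits the reach of the point to values that are truly missing.
- **The rule may not touch month 3.** It applies to follow-up evaluations. The Abstract calls month 3 the end point and keeps the follow-up points for months 6 and 12; Trial design can be read the same way. On that reading the superiority hypothesis, which is set within 3 months of treatment, is unaffected. The wording is ambiguous, so the month-3 part is conditional.
- **Some dropouts would be excluded instead.** This is true, but exclusion at discretion brings its own bias and does not repair the rule for those who remain.
- **Durability is not the aim.** The Discussion disclaims long-term effectiveness and calls all p-values exploratory. Month 6 is nevertheless listed as a time point of the primary outcomes.
- **Treatment may run to month 6.** The Primary outcomes section speaks of 6 months of therapy. If that holds, a month-3 value carried to month 6 does not cross the end of treatment, and the relapse argument is weaker there. This wording must be reconciled with the Abstract, Trial design and Group 1 sections.

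**Conclusion.** The concern holds in a limited form. The article makes last observation carried forward its only imputation rule, and where values are missing that rule replaces later symptoms with earlier ones and treats them as observed. The problem is clearest at months 6 and 12, provided treatment ends at about 3 months as most of the article says. Month-6 ENM success would then be overstated by 1.4 to 12.9 points under the assumed missingness and relapse.

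At month 3 the problem exists only on the wider reading of the rule. A reader might take the 6–10 points at 20% dropout as the bias in the trial's comparison. They are not: they are the inflation of one arm under assumed response rates. The matching shift in the difference is 3–5 points at 20% against 10% dropout and zero at equal dropout with equal rates, against a design difference of 30. Nor can it be said which arm gains, since the article gives no dropout, stopping or relapse rates and the rule carries failures forward as well as successes. The rule should be changed before analysis, but nothing here shows that the main comparison is invalid.

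**What to change.** Replace last observation carried forward in the Statistical analysis section.

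- **All outcomes:** use every observation collected after treatment stops. Do not carry a month-3 value forward unchanged to month 6 or 12.
- **Responder outcomes at months 3 and 6:** use multiple imputation. The model should include arm, HD/FC stratum, baseline, the available diary and questionnaire values, and whether treatment was discontinued. Discontinuation status is needed because a model built only on values before dropout would project the on-treatment course and repeat the fault. Enter HD/FC as a covariate, not as separate cells, since 39 per arm leaves few patients in each.
- **Sensitivity analysis:** pre-specify missing counted as non-response.
- **KINDL:** use a mixed model for repeated measures on baseline and months 3, 6 and 12, all already scheduled. It draws on month 3 through the estimated correlation, without assuming that the score stays the same.
- **Wording:** define which visits count as follow-up evaluations, and reconcile the 6 months of therapy under Primary outcomes with the treatment duration in the Abstract, Trial design and Group 1 sections.

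The cost is revised analysis wording and modest programming, with no new visits or patients. Intervals will be somewhat wider and response rates may be lower. If few children who stop are still observed, the imputation model will have little information about them, and the non-response analysis will matter more.

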## Materials and design

### Study objective and hypotheses

The aim of the study is to investigate the effects of SNM on symptoms and quality of life in children and adolescents. We intend to demonstrate that SNM is safe and effective in treatment of constipation and FI refractory to conventional therapeutic options.

The following hypotheses will be investigated within 3 months of treatment:(A)SNM is superior to ENM regarding treatment of abdominal pain as main symptom of refractory chronic constipation in childhood and adolescence.(B)Further exploratory hypotheses will be evaluated:SNM/ENM is effective and safe in reducing symptoms of chronic constipation and FI in children and adolescents as an additional therapeutic approach while continuing conventional treatment options unchanged.SNM/ENM treatment is effective in the subgroup of patients with Hirschsprung’s disease (HD).

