## Discussion

Neuromodulation is a promising approach in the treatment of chronic constipation and FI in children and adolescents. However, there is a substantial lack of well-planned, prospective clinical trials using an adequate sample size, appropriate methodology and validated outcomes to evaluate indications and efficacy in pediatric patients. Previously published outcomes of invasive and non-invasive sacral neuromodulation do predominantly not allow to draw firm conclusions because of small populations and high heterogeneity in outcome measures and participants. We were able to publish the first prospective randomized trial in 2022 on the efficacy of ENM (non-invasive SNM) in children and adolescents [11]. Patients, refractory to conventional treatment options, were included in the study and were randomized to either an optimization of these conventional options or to ENM under unchanged continuation of conventional options. We saw an improvement in outcome in 39% (conventional options alone) vs. 86% (ENM with conventional therapy, *p* < 0.0001). Conclusively, therapeutic efficacy of ENM could be shown, which serves as a baseline for this present study.

We here designed the study protocol of a prospective, monocentric, randomized 2-arm parallel-group trial, which to our knowledge is the first prospective, randomized study assessing SNM in pediatric patients and, above all, the first study assessing treatment differences between the invasive and non-invasive neuromodulatory approach (SNM vs. ENM).

We focused on determining appropriate sample size and reproducibility based on robust outcome variables. We also emphasized measurements to improve patient adherence, which is a challenge in pediatric clinical trials and especially regarding the use of self-administered therapy. The study design was therefore based on: (1) detailed information on mode of action, expected outcomes and self-administration for parents and in a child-centered approach for both, child and adolescent; (2) focus on the autonomous use of treatment by the child and the essential impact of parental monitoring; (3) individual documentation forms according to the age of the patient and separately for parents; (4) close monitoring to record treatment success and easy accessibility of the principal investigator/performing medical staff by e-mail for any problems that may arise.

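### No paired test is named for pre/post clinical outcomes, and two active open-label arms without sham cannot demonstrate that SNM or ENM is effective

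*Protocol article*

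**What the plan says.** Under Statistical analysis, clinical outcomes are compared by chi-square and Fisher's "exact tests at defined time points pre- and post-treatment in both groups". The next sentence does allow for pairing, but only for another endpoint: "Quality of life data is compared using unpaired or paired, two-tailed sample t-tests, if applicable". Primary outcomes and measurement defines the four primary variables as changes from baseline to 3 and 6 months in the same child, each with a success criterion.

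Study objective and hypotheses contains three statements of different strength:
- The aim: "We intend to demonstrate that SNM is safe and effective in treatment of constipation and FI refractory to conventional therapeutic options".
- Hypothesis A, between arms: "SNM is superior to ENM regarding treatment of abdominal pain as main symptom of refractory chronic constipation in childhood and adolescence".
- Hypothesis B, labelled exploratory and without a comparator: "Further exploratory hypotheses will be evaluated:SNM/ENM is effective and safe in reducing symptoms of chronic constipation and FI in children and adolescents". It extends to the Hirschsprung subgroup.

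Both arms receive active stimulation, and conventional treatment continues in both. The limitations in the Discussion concede that only sham stimulation could remove placebo bias, that patients and treating physicians are unblinded, and that the p-values are explorative.

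**The concern.** There are two separate problems.

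**Choice of test.** Chi-square and Fisher's exact test assume independent samples. A child's status before and after treatment is not independent, and no paired method is named for any clinical outcome. If the sentence covers within-arm comparisons, the test is wrong for them.

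**Attribution.** Hypothesis B and the aim speak of effectiveness, yet no randomised contrast in the trial isolates it. Within-arm change mixes any effect of stimulation with placebo response, regression to the mean in children enrolled while refractory, and continued care. A pre/post p-value could then be presented as proof that SNM, an invasive procedure, works in children. Randomisation protects only the SNM-ENM contrast.

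**Working it through.** **1. The plan's own figure.** Sample size calculation gives 39 per group for a 30% difference, α = 0.05, power 80%. The base rate is not stated; I assume 50% v 80%, two-sided, without continuity correction:

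n = [1.96·√(2·0.65·0.35) + 0.842·√(0.5·0.5 + 0.8·0.2)]² / 0.30² = 38.5, so 39.

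The figure reproduces as a between-arm calculation. It does not cover pre/post tests.

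**2. Effect of ignoring pairing (symptom present or absent, n = 39 in one arm).** The protocol gives neither the within-child correlation ρ nor the symptom prevalence, so both are assumptions. For prevalence p before and q after:

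- variance used by the unpaired test: [p(1−p) + q(1−q)]/n
- actual variance: [p(1−p) + q(1−q) − 2ρ√(p(1−p)q(1−q))]/n

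With p = q = 0.7 and ρ = 0.5 these are 0.42/39 and 0.21/39. The unpaired standard error is too large by √2, and the effective critical value is 1.96 × 1.414 = 2.77, a two-sided size of about 0.6%. Summing over all possible tables of 39 pairs gives 0.7%.

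Rejection rates from the same enumeration, nominal 5%:

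| Before → after | ρ | Chi-square (uncorrected) | Fisher | Exact McNemar |
|---|---|---|---|---|
| 70% → 70% | −0.2 | 7.8% | 4.4% | 3.0% |
| 70% → 70% | 0 | 5.3% | 2.7% | 2.9% |
| 70% → 70% | 0.3 | 2.1% | 0.9% | 2.4% |
| 70% → 70% | 0.5 | 0.7% | 0.2% | 1.9% |
| 70% → 50% | 0 | 44% | 35% | 35% |
| 70% → 50% | 0.3 | 43% | 32% | 46% |
| 70% → 50% | 0.5 | 42% | 29% | 61% |
| 80% → 50% | 0.3 | 86% | 77% | 88% |
| 80% → 50% | 0.5 | 90% | 81% | 99% |

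By symmetry, the 70% → 50% rows also hold for a rise from 50% to 70%. With positive correlation the unpaired tests are conservative, and the power loss grows with the correlation. For 80% → 50%, ρ = 0.5 is the largest value possible, because no child then worsens.

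**3. Attribution.** No arithmetic is needed here; the passages suffice. The arms are SNM and ENM, both active; conventional treatment continues; there is no sham or untreated arm. The Discussion reports an earlier randomised trial in which 39% improved on optimised conventional options alone and 86% on ENM plus conventional therapy. Substantial improvement without neuromodulation has therefore been seen by this group. A test of no change within an arm does not address whether the improvement exceeds what would have happened anyway, and pairing the test does not alter that.

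**The case against.** **The sentence may mean SNM against ENM at each time point**, where the tests are valid. The caption of Fig. 3, hypothesis A and the per-group sample size all fit that reading. This stands: the text is ambiguous. But on that reading no analysis is stated for hypothesis B, so clarification is needed either way.

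**The protocol is candid.** Hypothesis B is labelled exploratory, and the missing sham and explorative p-values are acknowledged. This also stands, and it narrows the point to the wording of the aim, which those admissions contradict.

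**ENM has cited controlled evidence** (86% v 39%), so superiority over ENM would indirectly support SNM. This is fair, but that support would come from the between-arm comparison, not from a pre/post test.

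**A reader might infer more.** Since success is defined as change from baseline, baseline responders number 0, and a pre/post Fisher test would be significant from 6/39 (p = 0.025), so that almost any response counts as effective. The documents do not support this. The protocol states no such test and no rule for declaring hypothesis B met. Nor is pairing the cause: exact McNemar also needs 6/39 (p = 0.031). Almost any response is also too strong, since at a true response of 5% or 10% the chance of reaching 6/39 is 1% or 19%. At 39% it would exceed 99.9%, which again points to the missing control.

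**A reader might also turn the 39% into a threshold**, for example requiring 22/39 so that the exact lower limit (39.6%) exceeds it. That is not supported either. The 39% comes from optimised conventional care, whereas here it continues unchanged; the article does not give that trial's denominators or outcome definition; and such a rule would treat 39% as known without error.

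**Conclusion.** The point holds in limited form. For clinical outcomes the protocol names only independent-sample tests and does not say whether they are meant between or within arms. If used within an arm on symptom presence, they err on the conservative side under positive correlation. The cost is power: about 19 percentage points for 70% → 50% and 9 for 80% → 50% at ρ = 0.5 (chi-square against exact McNemar), but only 2 to 3 points at ρ = 0.3. At zero correlation there is no loss. These sizes rest on assumed correlations and prevalences.

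The more important part rests on no assumption: two active open-label arms without sham cannot show that either treatment is effective, so the word demonstrate in the aim claims more than the design can deliver and contradicts the stated limitations. Hypothesis A and its sample size are not affected by this point.

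**What to change.** 1. State that the randomised SNM versus ENM comparison is the inferential analysis. Reserve chi-square or Fisher for it, or use a CMH test stratified by Hirschsprung's disease/functional constipation to match the randomisation.
2. Name paired methods for within-arm change: McNemar for binary outcomes, Wilcoxon signed-rank for episode counts.
3. Reword the aim and hypothesis B as description of within-arm change. Report each arm's month-3 response with an exact 95% confidence interval, and draw no conclusion of effectiveness from a pre/post p-value.
4. If the earlier trial's 39% and 86% are mentioned, label them non-randomised context for this trial, not a decision threshold.

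The cost is wording and a change of named tests; no additional patients or visits are needed. The price is a weaker claim for hypothesis B.
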